## Abstract

**Background:**

Exercise and physical therapy have been shown to be effective in the non-pharmacological symptomatic treatment of multiple sclerosis (MS). Hippotherapy as an additive physical therapy intervention is applied in this study to promote balance and postural control, since the number of sufficiently high-quality randomized controlled trials indicating its effectiveness is limited.

**Objective:**

This study aims to provide more in-depth insights into the effectiveness of hippotherapy in MS in terms of balance and other patient-relevant outcomes, building on the results of a preliminary study (MS-HIPPO II, evidence level 1b).

**Methods:**

Based on a prospective, randomized, investigator-blinded, controlled multicenter study design, the primary endpoint of differences in balance will be investigated. Patients will be randomized to an intervention group (12 weeks of hippotherapy) or a control group (12 weeks of treatment as usual). Balance will be measured using the Berg Balance Scale (BBS) plus a standardized balance task on a force plate (AccuGait-Optimized, Advanced Mechanical Technology, Inc., Massachusetts, US) and a balance perturbation task on an oscillating sensorimotor therapy device (Bioswing Posturomed®, Haider, Pullenreuth, Germany). During balance tasks, electrocortical activity will be investigated using electroencephalography (EEG) (LiveAmp 32, Brain Products GmbH, Gilching, Germany). Secondary endpoints include fatigue (FSS), quality of life (MSQoL-54), pain (VAS), spasticity (NRS) and participation (WHODAS 2.0). Therapy progress will be documented via an ICF-based hippotherapy assessment-tool (EQUITEDO®, Frechen, Germany).

**Results and conclusions:**

The results should contribute to improve the understanding of non-pharmaceutical treatment options in the field of exercise and movement therapy in MS.

**Trial registration:**

The trial was registered at March 05, 2024 in the German Clinical Trial Register under DRKS00033449.

## Introduction

1

For persons with multiple sclerosis (MS), perspectives on non-pharmacological symptomatic treatment have been increasingly investigated in recent years, in order to promote biopsychosocial functioning and maintain mobility [[1], [2], [3]]. To optimize health care beyond pharmacological therapy in outpatient treatment, MS represents one of 26 chronic conditions, where exercise is considered “medicine” [4]. In the development of the list of these 26 chronic conditions, cohesion for prescribing exercise as medicine was achieved on an evidence-based level [4,5]. It includes specific recommendations for type and dosage. Based on evidence of recent years, authors advocate exercise already at an early stage of MS, along with conventional medical treatment [6,7]. In this regard, physiologically oriented hippotherapy is practiced as a treatment for persons with MS, to improve movement processes by promoting the interaction of the central and peripheral nervous systems with the musculoskeletal system [8]. According to the German Federal Joint Committee (G-BA), hippotherapy is defined as physiotherapeutic treatment on a neurophysiological basis with and on a horse [9]. It is applied with the aim to counteract impaired or lost walking ability and to promote harmonious locomotion in a gait-physiologically correct movement pattern [8]. Specifically, the three-dimensional impulses from the horse's back in relation to centrifugal-, acceleration- and braking forces, e.g. by turns, gait changes or transitions, are expected to impact patients' body functions [8].

Prior studies have shown positive effects of hippotherapy in the complementary treatment of symptoms of MS, e.g. improving balance and postural control, reducing spasticity and self-perceived fatigue, increasing disease-related quality of life and function-related mobility [10,11]. In their systematic review focusing on motor functioning, Moutaftsis et al. [12] showed that hippotherapy had a positive impact on motor function, gait cycle (quality of walking), walking endurance performance, balance and orthostatic control. A further systematic review and meta-analysis by Suárez-Iglesias et al. [13] included 9 of 234 screened studies with sufficiently high methodological quality and confirmed previous evidence on improving static balance, fatigue and quality of life, but not the findings on gait quality and dynamic balance. In this context, the large number of studies not included in the reviews, indicates the widely diverging study quality of current investigations. The included studies had an average subject size of less than 30 patients (N = ⌀ 28.6), also different survey instruments were used and short therapy periods were evaluated, without follow-up assessments. The results of previous studies show, that despite the long-standing tradition of hippotherapy treatment in MS, there is still a lack of evidence of its efficacy based on randomized controlled trials (RCTs), study designs with sufficiently large sample sizes and studies with level 1 quality of evidence. The current study builds on the MS-HIPPO study (N = 70), which assessed the effectiveness of hippotherapy on the symptoms of MS, based on an RCT study design [11,14]. The two year study showed evidence of a positive effect of hippotherapy in MS patients at a high level of reliability (e.g. evidence level 1b) [11]. Central results showed that weekly hippotherapy, significantly improved balance performance (measured by BBS) as well as rapid fatigability (FSS), spasticity (NRS) and quality of life (MSQoL-54) in patients with MS [11].

## Methods

2

The aim of the current MS-HIPPO II study is to quantify the effects of hippotherapy on balance control in MS patients by means of state-of-the-art biomechanical and neurophysiological measurements. The effects of hippotherapy will be assessed in a larger number of cases (N = 140), on evidence level 1b via an RCT study design, also including a follow-up measurement. The follow-up assessment is intended to provide information on the persistence of potential effects.

The outcome measures used in the first MS-HIPPO study will be extended in this study to biomechanical, as well as neurophysiological measurements, such as cortical activity, during balance and balance perturbation tasks [14]. The primary hypothesis to be tested is:(1)Twelve units of hippotherapy significantly changes static balance performance, measured with the Berg Balance Scale (BBS) and a force plate, in the intervention group compared to the control group. Moreover, this change can also be sustained after the end of the intervention period (follow-up).

Secondary hypotheses are:(2)Hippotherapy significantly changes the neuronal correlates of balance performance, measured with electroencephalography, in the intervention group compared to the control group.(3)Hippotherapy leads to a change in MS specific symptoms such as spasticity, fatigue and pain in the intervention compared to the control group. Moreover, it is also expected that hippotherapy will positively influence motor functioning parameters, quality of life and participation in the intervention compared to the control group.

### Design

2.1

A randomized controlled trial design will be applied to obtain data from in total 140 subjects: (1) hippotherapy intervention group (IG) (approx. N = 70) and (2) control group (CG) (approx. N = 70). Within a project duration of two years and six months (01.01. 2024–30.06. 2026), both groups, IG and CG, are to be assessed during two separate study cycles with IG (N = 35) and CG (N = 35) in each study cycle. Each study cycle will consist of a twelve-week intervention period (1x hippotherapy/week) with a pre/post measurement and a six-week follow-up measurement (see Fig. 1). Before therapy begins, the population will be randomly and evenly assigned to one of two groups: IG or CG.

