### Screening and randomization

2.6

Participant recruitment will take place using a flyer in local media, at the study sites and at the supporting partner organization, German Multiple Sclerosis Society (DMSG) (Hannover, Germany). Subsequently, interested candidates can contact the scientific study team via telephone or email. An initial telephone interview will be conducted using a standardized script, where eligibility is checked according to the inclusion and exclusion criteria. Inclusion and exclusion criteria are similar to the criteria in the MS-HIPPO study and can be seen in Table 3, Table 4 [14]. If an inclusion is possible, patients will subsequently be referred to a study site physician, who will carry out an initial examination and approve a medical clearance. The patients included, will be informed about the study protocol and asked for their written consent. Patients can withdraw from the study at any time; medically relevant withdrawals are forwarded to the monitor and responsible ethics committee. After initial contact, written informed consent and medical clearance of the participants, they will be randomly assigned to IG and CG. The allocation sequence will be generated by computer-generated random numbers. Individuals are randomized stratified by location, gender distribution of the disease and Expanded Disability Status Scale (EDSS) [34]. A code-generated random mechanism will be used for concealment. Scientific study personnel will generate the allocation sequence, enroll participants, and assign participants to interventions based on a stratified adaptive randomization.

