### Statistical procedures

2.8

The sample size was estimated on the basis of the primary outcome measure, the relevant effect size and the planned statistical test procedures. Statistical results of preliminary study MS-HIPPO showed a large effect in the per-protocol population with a change of 4.61 points in BBS between the IG and CG (95 % CI: .74–7.47, p = .002, N = 41) [11]. As individual-level baseline data were not available, a baseline–post correlation could not be calculated, and the sample size was therefore estimated based on the large empirical effect observed in the MS-HIPPO trial. Sample size was determined with G∗Power (Heinrich Heine University Duesseldorf, Germany, version 3.1.9.7) for the statistical F-test ANCOVA with two groups and five covariates, assuming an effect size of f = .40 (α = .05, 1–β = .80). This resulted in N = 111 (df = 104, actual power = .80), which was inflated to N = 140 to account for an anticipated 20% attrition rate, for the primary analysis model [35], consistent with methodological recommendations in clinical research using the standard factor ( *Nplanned* = 111 ÷ (1 − .20) = 139 ≈ 140), [11,36].

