The study represents a confirmatory analysis, but due to the in-depth biomechanical and neurophysiological experimental measurements, the sample size calculation also includes a calculation of an additional sub-sample for the experimental protocol. In addition to the assessments listed in Table 7, they subsequently completed the balance tasks on the force plate and oscillating sensorimotor therapy device at each of the three measurement timepoints (see Table 6). In order to protect the patient collective of the study and avoid increased drop-out due to complex biomechanical and neurophysiological measurement technology, a reduced sample size was calculated on the basis of the effect strength of the preliminary study [11,14]. According to the effect size calculations of the Institute for Medical Statistics and Bioinformatics at the University of Cologne, the mean difference in BBS of 3.07 points (standard deviation (SD) = 1.04) of the IG and CG for a type 1 error rate of α = 1 % and a power of 1-β = 95 %, a required minimum sample size of N = 44 was calculated for the statistical F-test ANCOVA (fixed effects, main effects and interactions, two groups and five covariates) (95 % CI: 1.00–5.14, p = .004) assuming an effect size of f = 1.47 (df = 36, actual power = .95) [11,35]. Based on the ≈40 % drop-out rate of the preliminary study (N = 70) PP analysis (N = 41), a total of 70 patients (2x35) shall be randomized for in depth-biomechanical and neurophysiological measurements (during balance task and balance perturbation task) with a drop-out rate of around 40 %, to ensure a sufficient number of cases for this more extensive analysis [11]. Statistical evaluations will be carried out using the programs IBM SPSS 29 (IBM, Ehningen, Germany), R-Statistics (R Foundation, Vienna, Austria), JASP (JASP Team (2024), JASP (Version 0.19.3) [Computer software]) and Python [37]. Statistical methods for analyzing the primary outcome of change in balance performance after 12 units of therapy (change from baseline) will be covariance analyses (ANCOVA) (95 % confidence interval). The data will be analyzed with regard to an anchor-based approach of the minimal clinically important difference (MCID) of the BBS in individuals with MS (3 points according to Gervasoni et al., [38]. These analyses shall be verified by sensitivity analyses using linear mixed models (LMMs). Via this approach, incorporate fixed and random effects are being calculated to accurately represent non-independent data structures, to capture the change over the duration of therapy and follow-up. Therapeutic facility, gender, age, baseline BBS and EDSS score are included in the calculations as co-variables. This approach accommodates missing data under the missing at random (MAR) assumption, ensuring that all available measurements are included and therefore provide less biased and more robust estimates.

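### Study cycle is missing from the covariate list although equal arms are planned within each of two cycles: a minor, nearly free loss of precision

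*Protocol article*

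**What the plan says.** Under Design, the protocol article plans 140 patients, about 70 per arm, and states that the arms "are to be assessed during two separate study cycles with IG (N = 35) and CG (N = 35) in each study cycle". The same paragraph says that before therapy begins "the population will be randomly and evenly assigned to one of two groups: IG or CG".

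Under Screening and randomization, the stratifiers are named: "Individuals are randomized stratified by location, gender distribution of the disease and Expanded Disability Status Scale (EDSS"). Cycle is not among them.

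Under Statistical procedures, the methods for the primary outcome, change in BBS from baseline, "will be covariance analyses (ANCOVA) (95 % confidence interval"), with linear mixed models as sensitivity analyses. The adjustment set is then given explicitly: "Therapeutic facility, gender, age, baseline BBS and EDSS score are included in the calculations as co-variables". That sentence follows the mixed-model text. Its five items match the sample-size calculation, which was done "for the statistical F-test ANCOVA with two groups and five covariates", so it is fair to read it as the ANCOVA list too. Cycle is not in it.

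**The concern.** The trial runs as two separate cohorts within a project of two and a half years, and the plan aims for equal arms within each. All three named stratifiers (location, gender, EDSS) are in the model. Cycle is the one other factor on which equal arms are planned, and it is left out.

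Equal arms within cycle keep a cycle effect out of the treatment estimate. They do not keep it out of the estimated error. Variation between cycles that the design removes from the arm comparison is still counted as residual variance when cycle is not modelled, so the reported standard error is larger than it should be.

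If equality within cycle is not achieved, or is lost through drop-out, part of a cycle effect can also enter the estimate. Drop-out that differs by arm is conceivable: the protocol anticipates 20% attrition, reports about 40% in the earlier trial, and has a minimum-attendance rule for hippotherapy sessions that can apply only to the intervention arm.

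At stake is a small amount of precision, and some protection against chance or attrition imbalance.

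**Working it through.** **Inputs from the protocol.** Two cycles, 35:35 in each (Design). Five covariates, two groups, N = 111 and error df = 104 before attrition (Statistical procedures).

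**Input assumed.** D, the difference between cycles in 12-week BBS change after adjustment for the five covariates, in residual SDs. The document gives no value, so D runs from 0 to 1.0.

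**The plan's own figures.** The protocol plans the sample size "assuming an effect size of f = .40 (α = .05, 1–β = .80") and reports "This resulted in N = 111 (df = 104, actual power = .80").
- Error df = N − groups − covariates = 111 − 2 − 5 = 104, as stated.
- Attrition: 111 / (1 − 0.20) = 138.75, taken as 139 and then 140, as stated.
- N = 111 itself does not reproduce for a two-group contrast. With one numerator df, f = 0.40, α = 0.05 and power 0.80, the noncentral F gives N = 52 (error df 45, power 0.806). N = 111 with df = 104 appears only with ten numerator df. That is a separate and larger matter. It bears on this point only because it affects which power figures apply below.

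**Standard error when cycle is omitted.** Two equal cycles that differ by D add D²/4 to a residual variance of 1. The SE ratio is √(1 + D²/4). The equivalent share of the sample lost is 1 − 1/(1 + D²/4).

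**Interval width at N = 111.** Allowing for the degrees of freedom, the ratio of widths without and with cycle is √(1 + 111·D²/(4·104)) × t(104)/t(103), with t quantiles 1.9830 and 1.9833.

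| D (assumed) | 1 + D²/4 | SE ratio | Sample equivalent lost | Interval width ratio |
|---|---|---|---|---|
| 0 | 1.0000 | 1.000 | 0% | 1.000 |
| 0.2 | 1.0100 | 1.005 | 1.0% | 1.005 |
| 0.3 | 1.0225 | 1.011 | 2.2% | 1.012 |
| 0.5 | 1.0625 | 1.031 | 5.9% | 1.033 |
| 0.8 | 1.1600 | 1.077 | 13.8% | 1.082 |
| 1.0 | 1.2500 | 1.118 | 20.0% | 1.125 |

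A simulation (4,000 runs, N = 112, arms equal within cycle) gave width ratios of 0.999, 1.005, 1.031 and 1.120 for D = 0, 0.2, 0.5 and 1.0. At D = 1.0, coverage of the nominal 95% interval was 96.9% without cycle and 94.7% with it. The omission therefore errs on the conservative side.

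**Power at N = 111, one numerator df, cycle variance treated as ordinary noise.**
- At the stated f = 0.40: 98.7% with cycle; without it 98.6%, 98.2% and 96.2% for D = 0.2, 0.5 and 1.0.
- At f = 0.268, where N = 111 gives about 80%: 79.9% with cycle; without it 79.5%, 77.5% and 70.6%.

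These losses are slightly overstated if the arms are exactly equal within cycle, because the estimate then carries no cycle variance and only its reported SE does. For f = 0.268 and D = 0.5, a normal approximation gives Φ(0.268·√111 − 1.033 × 1.983) = Φ(2.824 − 2.048) = Φ(0.776), about 78%.

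**Shift in the estimate if the arms are unequal by cycle.** The bias is roughly D times the difference between arms in the share of patients from one cycle. With an assumed D of 0.3 and a 10-point difference, that is 0.3 × 0.10 = 0.03 SD.

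**Cost of including cycle.** Error df falls from 104 to 103. At D = 0 the interval width is unchanged to three decimals.

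**The case against.** The strongest case against is that the plan already adjusts for every stratifier it names, and cycle is not one of them. The 35:35 figure is an enrolment plan in a paragraph that itself says approximately 70 per arm. Nothing says that allocation is blocked by cycle. This stands. A reader might infer that cycle restricts the randomization just as site, gender and EDSS do, and that leaving it out breaks the rule of analysing as randomized. The document does not support that. The argument for including cycle does not depend on it: if 35:35 is achieved, adjustment recovers precision, and if it is not, adjustment guards against imbalance.

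A reader might also infer that every difference between the cycles ends up in the error term. It does not. Differences in baseline BBS, age, EDSS, gender or site mix are taken up by the listed covariates. Only a remaining difference in BBS change matters.

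Whether such a difference exists is unknown. Season, change of assessors and growing therapist experience are possible causes, not documented ones. The protocol describes certified sites, a manual and trained assessors. Therapist experience would act mainly in the intervention arm, as a treatment-by-cycle interaction, which a main effect for cycle removes only in part.

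The upper rows of the table are hard to believe. For two equal groups, f = 0.40 is a standardized difference of 0.8, so D = 0.8 would mean that cycle moves BBS change as much as the planned treatment effect.

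Finally, a condensed article may leave some covariates to a fuller document. That carries less weight here, because the article states a definite list of five and sizes the trial on five.

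**Conclusion.** The point holds as a minor precision improvement. Equal arms are planned within two cycles, and cycle is absent from an explicit covariate list. If a cycle difference in BBS change remains after adjustment, the interval is wider than necessary: by 0.5% to about 3% for differences of 0.2 to 0.5 residual SD, and by about 8% for an unlikely 0.8. If the arms become unequal by cycle, a small shift in the estimate is also possible.

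All of this rests on an assumed cycle effect. If there is none, nothing is lost. It would go too far to say that power is certainly lost, or that the primary analysis is wrong: without cycle and with arms equal within it, the ANCOVA is valid and, if anything, slightly conservative.

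**What to change.** Add study cycle (1 or 2) as a fixed two-level factor to the covariate list for the primary ANCOVA, the analogous secondary ANCOVAs and the linear mixed model. Cycle is known for every patient, so no data collection changes. The cost is one entry in the list and one of about 104 error degrees of freedom. Fixing it before the data are analysed also avoids a post hoc choice in a trial described as confirmatory.

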**Fig. 1 fig1:**
[figure not shown]
Study design.

### Study sites

2.2

The study will be conducted at 8 study sites in Germany (see Table 1). Hippotherapy is carried out according to the methodology of the German Curatorship of Therapeutic Riding e.V. (DKThR), which ensures quality of therapeutic measures, animal welfare and standardization [15]. All facilities fulfill the requirements for study sites shown in Table 2 and are certified facilities for hippotherapy (DKThR)® by DKThR.

**Table 1 tbl1:** Study sites.

Study sites
Center for Therapeutic Riding Johannisberg e.V., Windhagen
Center for Horseriding and Equine assisted Therapy, Carolinenhof, Essen
Center for Therapeutic Riding, Nuetzen
Equestrian Sports and Therapeutic Riding Center of Gold Kraemer Foundation, Frechen
HPZ Wolfgang Fahr Therapeutic Riding Ltd., Ostfildern
Riding Center Children's Aid, Ludwigshafen
Inclusive Equestrian Sports and Therapeutic Riding Center Karlshorst, Berlin
Gut Wittmoldt (estate), Wittmoldt

**Table 2 tbl2:** Requirements for study sites.

Requirements study sites
DKThR-certified facility^a^ [16]
Implementation of hippotherapy according to the guidelines of the DKThR® [15]
Designation of the lead hippotherapist and a coordinator
Appointment of the responsible physiotherapist and his/her deputy
Separate room for baseline, post and follow-up assessments
At least 2 trained therapy horses must be available for the therapy
At least 6 patients must be treatable per week
Comprehensive cooperation with the monitor

a German Curatorship of Therapeutic Riding e.V. (DKThR) represents the national federation for equine-assisted therapy, rehabilitation and equestrian sports for persons with disabilities. The association comprises the fields of medicine, psychotherapy, psychology, education and sport [17].

